### Participants

We will recruit about 200 participants from six HIV treatment centers in Botswana. These treatment centers were selected strategically to include the two largest referral hospitals serving the northern and southern ends of Botswana. As referral hospitals, they service PLH from different parts of the country, thus giving the study an increased likelihood of recruiting participants from various backgrounds.

Recruitment of participants will be conducted using a short initial screening during their regular visits to the HIV medical staff. Further screening will be done by the researchers. The inclusion criteria for participation in the study are as follows: being HIV positive, presenting with mild to moderate depressive symptoms (that is, a score greater than 4 and less than 20 on the Patient Health Questionnaire 9 (PHQ-9) [26], aged 18 years and older, having sufficient knowledge of the Setswana or the English language, and available for the next 8 weeks to work on the intervention. The exclusion criteria are as follows: (almost) no symptoms of depression (a score of 4 or less on the PHQ-9), presenting with severe cognitive impairments (medical staff and coaches to use their clinical judgement to determine if the patient may be presenting with severe cognitive deficits), being in the first 6 months post-HIV diagnosis, and suicidality as determined by a score of > 1 on the suicide item of the PHQ-9. Those who score within the severe depressive symptoms range (≥ 20) or suicide ideation as measured by the PHQ-9 will be referred for face-to-face psychological or psychiatric treatment or to a medical doctor at the treatment center.

### Sample size

To determine the sample size needed for the RCT, we performed a power analysis using the 14th Edition of the Power Analysis and Sample Size Software (PASS) [27]. It was calculated that each group should consist of 64 participants (effect size = 0.50, alpha = 0.05, and power = 0.80). Similar studies have recorded a dropout rate of 15%; therefore, at least 75 participants should be allocated to each group. Taking into account the possibility of further dropout at follow-up, a total of 200 participants will be recruited for the RCT.

### Procedure

The study design flowchart is presented in Fig. 1. We will start by providing information about the study, screening guidelines, and forms to the treatment centers. Participants will be screened for depressive symptoms by the HIV nursing consultants and doctors during their regular check-ups at the treatment centers using the PHQ-2 questionnaire. Participants will also be screened for meeting the inclusion criteria (age 18+, HIV diagnosis longer than half a year, access to a telephone, ability to read/understand English or Setswana well, no severe cognitive limitations, such as severe forgetfulness or mental confusion, and no current treatment by a psychologist or psychiatrist at this moment) with the use of a short checklist.

**Fig. 1 Fig1:**
[figure not shown]
Flowchart of the study design

In Botswana, the majority of patients who have been on treatment for more than a year visit the treatment center once every 6 months; therefore, the screening will be conducted over a period of approximately 6 months. Any patient who obtains a score > 0 on the PHQ-2 and who meets the inclusion criteria may be referred to the researchers. The HIV consultants will provide written information about the study to the patients and request for permission to provide the researchers with the patient’s contact information (telephone number or email). Following contact with the patients, the researchers will provide further information to the patients and conduct extensive screening for depressive symptoms using the PHQ-9 by telephone. Patients with a score within the mild (> 4) and moderate (< 20) ranges will be eligible for participation in the trial. These patients will then be invited to participate. Those who agree to participate will give consent by a text message to the researchers. Additionally, we will seek permission from patients to inform a medical doctor or general practitioner at the HIV treatment center about their participation in the study. Participants will then undergo a pre-test (T0). Thereafter, the participants will be randomly assigned to the intervention or the control (attention-only) group. The coaches will call all participants at the beginning of the intervention to assess for and stimulate their motivation. This will be accomplished through the use of motivational interviewing and general conversational techniques, providing information about the program, helping the patients plan for the lessons, and advising them to engage in a small activity to get started.

The intervention group will then receive the self-help treatment program with coaching by telephone, while the control group will only receive attention through a weekly telephone chat from a coach. The participants will work on the intervention for 6 weeks (with a maximum extension of 2 weeks). During the intervention, participants will be asked to answer standardized questions at three different times. At 8 weeks, all participants will complete the post-test (T1) and subsequently the follow-up measurement (T2) 3 months later. After the follow-up, participants in the control condition will receive the intervention.

The pre-test, post-test, and follow-up assessments will be done by the researchers through a standardized telephone interview; the three assessments during the intervention will be done during the coaching sessions, after the completion of lessons 1 (activation), 2 (physical relaxation), and 4 (changing negative thinking patterns). Callers will follow a standard script where they will explain who they are and the purpose of the interview. Participants will be asked questions exactly as they appear on the questionnaire. The answer categories for each section will be called out, and the participants will be asked to write them down for easy reference. Callers are allowed to repeat questions at the request of the participant.

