### Study conditions: booklet self-help intervention

The booklet self-help with coaching intervention employs cognitive behavioral therapy (CBT) and stress management techniques and is based on self-regulation and stress-coping theories [28]. The content of the self-help program contains the following main components: activation, relaxation, changing maladaptive cognitions, and the attainment of new personal goals. This content is covered over six lessons to be completed in a maximum of 8 weeks and uses a combination of psycho-education, assignments, and exercises. To reduce attrition over time and to keep participants motivated, coaches will offer support and motivate participants.

The participants receive the intervention in the form of a booklet and will work on the program 1–2 h every week for 6 weeks. The first lesson is an introduction to the program and focuses on activation. Participants will be asked and encouraged to think of a small concrete new activity to perform. Throughout the program, participants will be encouraged to continue thinking about small concrete new activities to perform. Lesson 2 will be cover physical relaxation. Participants are taught to do some relaxation exercises that they continue with for the rest of the program. The third lesson will focus on changing negative thoughts. Participants are trained to recognize and change their negative thinking patterns. In lesson 4, participants will learn strategies to stop unpleasant thoughts whenever they want (for instance, by using a positive feeling). In lesson 5, participants will be helped to find new, meaningful, concrete, and time-bound life goals. They will be guided to work on attaining their goals. The last lesson will focus on achieving self-confidence to achieve their goals. Participants will learn to challenge negative thoughts which prevent them from working on their goals and gain confidence to achieve their goals. The program concludes with a summary of the important tips and tricks.

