### Support from a coach

A coach will be allocated to each participant to provide support and motivation for the duration of the program. At the beginning of the program, the coaches will make telephone contact with the participants to introduce and explain technical aspects of the program and provide motivation. The coach will also schedule a weekly telephone call with the participant that will last approximately 15 min. During the telephone call, the coach will enquire about the progress of the participant and problems encountered and will offer support and motivation as well as encourage the participant to continue working on the program. Coaches follow a script to interview patients. Furthermore, coaches will be asked to record their telephone calls and also note what they discussed with the patient after every call. The audio recording and notes will be used to check if the coach follows protocol during supervision with the researchers and/psychologist. No formal psychotherapy will be provided to the participants by the coaches. During the telephone calls, the coach will provide support and motivation by enquiring about the participant’s progress, making motivational statements, and listening and providing guidance in case the participant is facing any problems. Six telephone coaching sessions will be provided in total, connected to each of the six lessons. The participant is expected to complete the program in 6 weeks, with a maximum extension to 8 weeks. If a participant has not completed the program after 8 weeks, he/she is allowed to continue with the program; however, the coaching will stop.

In the control condition, all participants will only receive minimal support in the format of six telephone calls by a coach over a period of 6–8 weeks. The weekly telephone calls between coaches and participants in the control condition will last for approximately 5 min. During this telephone call, the coaches will enquire about the participant’s well-being. Coaches will monitor the depressive symptoms of the participants and try to prevent participant dropout by helping them to explore solutions to the obstacles they face with the program, discussing the pros and cons of quitting, and continuing to make motivational remarks.

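### As written, the opening coach call after randomisation gives the attention-only control arm programme information, lesson planning and activity advice, contrary to the control's own definition

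*Protocol article*

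**What the plan says.** The Procedure section of the protocol article gives a sequence. After the pre-test comes allocation: "Thereafter, the participants will be randomly assigned to the intervention or the control (attention-only) group". The next step is the opening call: "The coaches will call all participants at the beginning of the intervention to assess for and stimulate their motivation". Its content follows: "This will be accomplished through the use of motivational interviewing and general conversational techniques, providing information about the program", and then "helping the patients plan for the lessons, and advising them to engage in a small activity to get started". Only in the following paragraph do the arms separate: "The intervention group will then receive the self-help treatment program with coaching by telephone, while the control group will only receive attention". For controls, that attention comes by way of a weekly telephone chat with a coach.

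The section Study conditions: booklet self-help intervention names activation first among the main components. Of Lesson 1 it says: "Participants will be asked and encouraged to think of a small concrete new activity to perform". The Assessments section lists activation, measured by one item, among the mediators.

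Support from a coach describes an opening contact that introduces the programme and motivates the participant, within its account of coaching for the programme. It then limits controls to minimal support: six calls of about 5 minutes, with an enquiry about well-being, symptom monitoring, efforts to prevent dropout and motivational remarks. Within that control text, however, coaches are described as "helping them to explore solutions to the obstacles they face with the program". Design and Procedure both say that controls receive the programme only after the follow-up measurement.

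**The concern.** The comparator is described in two ways that do not agree. One description is attention only. The other is attention preceded by a call that carries elements of the tested programme. Coaches working from the Procedure text would be following the protocol if they briefed a control participant on the programme, tried to plan lessons with that person, and advised a small new activity.

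Two things are at stake. First, content shared between arms tends to pull them together, so the estimated effect on depressive symptoms would lean towards no difference. Second, the overlap falls on activation, so separation on a variable the trial means to study as a mechanism could also shrink. Apart from any bias, the results paper could not describe accurately what the control arm received.

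**Working it through.** The protocol gives no figure for this point, so the check is a comparison of passages.

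1. **Timing.** In Procedure the order is pre-test, random assignment, opening call, then divergence of the arms. The call therefore follows allocation and could have been made specific to each arm.

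2. **Recipients.** The call is addressed to all participants. No section restricts it to the intervention arm.

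3. **Content against the control definition.**
   - Motivation: Support from a coach allows motivational remarks in the control calls, so this element is not clearly in conflict.
   - Programme information: conflicts, because controls have no programme during the comparison period.
   - Lesson planning: conflicts, because controls have no lessons to plan.
   - Advice to start a small activity: goes beyond an enquiry about well-being, and closely resembles the Lesson 1 task quoted above.

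4. **How long controls are without the programme.** Procedure puts T1 at 8 weeks and T2 three months later. Eight weeks is roughly two months, and 2 + 3 gives about five months before a control participant receives any lesson. The control-call wording about obstacles with the programme therefore has nothing to refer to in that period.

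5. **Scale of the possible overlap.** Using the contact figures in the intervention and coach-support sections:
   - Intervention arm: 6 coaching calls × about 15 min = about 90 min, plus 6 weeks × 1–2 h = 6–12 h of work on the booklet.
   - Control arm: 6 calls × about 5 min = about 30 min.
   - Opening call: length not stated, and the text does not say whether for controls it is one of the six calls or an additional one.

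   The overlap is thus part of a single call set against 6–12 h of self-help and about 90 min of coaching. This shows that the shared content is a small share of the programme. It does not convert into an effect on the depression scores.

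**The case against.** The strongest reply is that the phrase is loose. The article often writes of participants when it can mean only the intervention arm. Procedure itself goes on to say that the participants work on the intervention for 6 weeks, which cannot include controls. Lesson planning makes no sense for someone without a booklet, and Support from a coach places the opening contact in its account of programme support. The sentence on obstacles appears in a passage about preventing dropout, and the Dropout section counts loss of interest in the questionnaires as well as leaving the intervention. The programme may there simply mean the study. Scripts and a protocol for coaches are mentioned but not shown, and may already differ by arm.

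This is a possible reading, and it rules out treating contamination as established. It does not remove the point: the order of allocation, call to all, then divergence favours the literal reading, nothing limits the call to one arm, and the published wording is wrong on either reading.

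It could also be argued that a shared motivational start is a legitimate design and that any resulting bias is conservative. That holds for motivation, which the control definition already permits. It does not cover lesson planning or activity advice in an arm defined as receiving attention only.

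A reader might go further and attach a loss of power. With 85 per arm (100 less 15% dropout), two-sided alpha 0.05 and a two-sample t-test, power is 90% at a standardised difference of 0.50, 83% at 0.45 and 74% at 0.40. But the documents give no basis for supposing that one call moves controls by 0.05 or 0.10 SD, so these figures are no estimate of harm. A reader might also infer that controls told of lessons they must wait for would be disappointed and drop out more often. That is speculative: participants are unblinded and informed about the study before consent in any case, and nothing ties such an effect to this call.

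**Conclusion.** The inconsistency is real and should be corrected. As worded, the opening call delivers programme information, lesson planning and activity advice to both arms after randomisation. This conflicts with the stated control condition and overlaps with the activation content of Lesson 1. The control-call text repeats the problem on a smaller scale by referring to a programme that controls do not yet have.

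If followed literally, the expected direction is a narrower contrast on depressive symptoms and on activation. The size cannot be derived from the documents and may be small. The conclusion rests on reading the recipients of the call as stated. If the intended recipients were the intervention arm only, what remains is a drafting error that coaches could still act on. The documents do not support saying that controls will in fact be exposed, or that the trial loses a given amount of power.

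**What to change.** Reconcile Procedure, Study conditions and Support from a coach by stating the content of the opening call separately for each arm. Confine programme information, lesson planning and activity advice to the intervention arm. Describe the control version in the terms the protocol already uses for that arm: enquiry about well-being, symptom monitoring, and motivational remarks aimed at staying in the study. State whether the opening call counts among the six control calls.

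Reword the control text in Support from a coach so that obstacles and quitting refer to study participation and assessments, not to the programme. Use the call recordings already planned for supervision to check that each arm receives its own version.

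The cost is a second call script and a short point in coach training, with no extra calls or staff. Trial status reports that recruitment had not begun and that trial materials were still being translated, so the change can be made before any participant is called.

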## Methods/design

### Design

To evaluate the effectiveness of an intervention recently developed for PLH in Botswana, an RCT will be performed. The trial will have two conditions: an intervention group, who will receive the self-help program with coaching for depressive symptoms, and an attention-only control group, who will receive the self-help program without coaching following completion of the follow-up measurement. Random allocation of participants to the intervention or control group will be performed using a stratified random sampling technique. The sample will be stratified according to gender and treatment center. It is important to stratify by gender to ensure approximately equal proportions of males and females in the intervention and control groups. In the study by [name] et al. that investigated intervention targets for depressive symptoms among PLH in Botswana, more females participated compared to males. Additionally, treatment centers are expected to differ with regard to the number of patients included; therefore, stratification will ensure that both the intervention and control groups in large and small treatment centers have almost the same numbers of patients in both conditions.

Random number tables will be used to allocate participants to either condition; these will be computer generated and produced by an independent researcher. Randomization will be done in permuted blocks of six. The independent researcher will enter the numbers into an Excel file which will conceal the randomization until after the participants are established in the trial. The randomization is set up such that the main researcher is unable to see treatment allocation beforehand, minimizing bias. Participants and coaches will not be blinded to allocation to conditions. Participant allocation to one of the conditions will be done after the pre-test.

The study is approved by the Health Research Development Committee of the Ministry of Health in Botswana (Ref. HPDME 13/18/1). The Standard Protocol Items: Recommendations for Interventional Trials (SPIRIT) checklist is provided as Additional file 1.

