The coaches will follow guidelines on the protocol regarding provision of support and motivation. All coaches will be trained in the study procedures, and they will be expected to record each telephone call conversation and the elements used during the call such as motivation and support. Coaches will be students with a minimum of a Bachelor of Psychology degree and will have completed a clinical course during their training and been taught communication skills, interview techniques, and treatment strategies. Personal interviews will be held before coaches are appointed, and only those coaches with adequate communication skills and the capacity to provide support and motivation will be selected. Selected coaches will be provided with extra training, such as motivational interviewing skills. The researchers and a licensed psychologist will supervise the coaches. In the first month of the study, the main researcher and the coaches will hold meetings every week to discuss any challenges they are facing. Thereafter, meetings will be held every 2 weeks. Should problems arise during meetings between the coaches and the main researcher, the responsible psychologist will be contacted.

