### Assessments

The data will be collected at six different times during the trial (T0, three in-between assessments during the intervention, T1, and T2). Table 1 shows each stage of the study and the assessments that will be used. The initial screening (PHQ-2) will be done at the treatment centers by HIV nursing staff and doctors. At T0, T1, and T2, the researchers will conduct the assessments via a standardized telephone interview. The three in-between assessments will be conducted by the coaches by telephone.

**Table 1 Tab1:** Summary of assessments for the study

Assessment	Screening HIV treatment centers *(+/− 5 min)*	Screening researchers *(+/− 10 min)*	T0: pre-test *(+/− 25 min)*	Three times during intervention/waiting period^1^ *(+/− 10 min)*	T1: post-intervention/waiting period: 6–8 weeks after T0^1^ *(+/− 20 min)*	T2: 3 months follow-up *(+/− 20 min)*
PHQ-2	X	–	–	–	–	–
PHQ-9	–	X	X	–	X	X
CES-D	–	–	X	–	X	X
Demographics and other information	–	–	X	–	X	X
Physical tension questionnaire	–	–	X	X	X	X
BADS	–	–	X	X	X	X
CERQ-short	–	–	X	X	X	X
Self-efficacy questionnaire	–	–	X	X	X	X
Goal Disengagement and Reengagement Scale	–	–	X	X	X	X
BERQ	–	–	X	–	X	X
GAD-7	–	–	X	–	X	X
PHQ-4	–	–	–	X	–	–
Life Events Scale	–	–	X	–	X	X
Motivation	–	–	X	–	–	–
Social support	–	–	X	–	X	X
Alcohol and substances	–	–	X	–	X	X
Compliance	–	–	–	X	X	–
Dropout	–	–	–	X	X	–
User satisfaction questionnaire	–	–	–	–	X	–

*PHQ-2* Patient Health Questionnaire 2, *PHQ-9* Patient Health Questionnaire 9, *CES-D* Center for Epidemiological Studies Depression Scale; BADS = Behavioral Activation for Depression Scale, *CERQ* Cognitive Emotion Regulation Questionnaire, *BERQ* Behavioral Emotion Regulation Questionnaire, *GAD-7* Generalized Anxiety Disorder 7, *PHQ-4* Patient Health Questionnaire 4

^1^Not asked to participants in the control group

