To measure depressive symptom severity (primary outcome), we will use the PHQ-9 [26] and the Center for Epidemiological Studies Depression Scale (CES-D) [29]. Secondary outcomes include physical tension (physical tension questionnaire), activation (Behavioral Activation for Depression Scale (BADS) [30]), cognitive coping (Cognitive Emotion Regulation Questionnaire-short (CERQ-short) [31]), behavioral coping (Behavioral Emotion Regulation Questionnaire (BERQ) [32]), symptoms of anxiety (Generalized Anxiety Disorder 7 (GAD-7) [33]), negative life events (Life Events Scale [34]), self-efficacy ([name] and [name], “Self-efficacy questionnaire,” unpublished), goal reengagement [35], social support, alcohol and substance abuse [36], and demographic variables. Some of the measures are single-item questions that are based on the original scales. The items were selected based on item-total correlations from our earlier research that investigated prevalence and risk factors of depressive symptoms of PLH in Botswana ([name] et al., “Depressive symptoms among people living with HIV/AIDS in Botswana: a search for intervention targets for a coping-skills intervention,” submitted). We will also measure the participants’ motivation to start the intervention, compliance, dropout and reasons for the dropout, and user satisfaction.

Through a self-designed questionnaire, we will collect information on demographic characteristics (such as age, gender, and level of education) and clinical and psychological characteristics (such as age, depressive symptoms severity, physical health, HIV status, alcohol and substance use, motivation, and social support) as potential moderators of treatment. We will measure treatment mediators and depressive symptoms (dependent variable) during the intervention as well as during the waiting period for the control condition. The following mediator variables will be assessed in the study: physical tension (one item), activation (one item), coping (four subscales from the CERQ-short: rumination, catastrophizing, positive refocusing, and refocus on planning), self-efficacy (one item), and goal reengagement (six items). This makes it possible to examine which mechanisms precede change in the primary outcome.

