#### User satisfaction questionnaire

A self-designed questionnaire with 31 open and close-ended questions will be used to collect information regarding participants’ satisfaction with the self-help program as well as their coach. The questionnaire will ask participants to evaluate the intervention as well as the support received from the coach assigned. Participants in the control condition will be asked 11 questions to evaluate their support from the coaches only. The responses will help in adjusting the program where necessary.

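### T1 and T2 interviewers may know the allocation when they collect the primary outcome: the same role supervises the coaches, and the T1 call contains arm-specific questions

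*Protocol article*

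**What the plan says.** Outcome collection. Procedure says: "The pre-test, post-test, and follow-up assessments will be done by the researchers through a standardized telephone interview". Assessments repeats it: "At T0, T1, and T2, the researchers will conduct the assessments via a standardized telephone interview". On the outcome itself it says: "To measure depressive symptom severity (primary outcome), we will use the PHQ-9", together with the CES-D. Table 1 schedules both scales at T0, T1 and T2.

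Supervision. Under Support from a coach: "The researchers and a licensed psychologist will supervise the coaches". The same section says of the coaches' calls: "The audio recording and notes will be used to check if the coach follows protocol during supervision with the researchers and/psychologist". It adds that the main researcher meets the coaches weekly in the first month and every 2 weeks after that.

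Arm-specific content at T1. Table 1 places compliance and user satisfaction at T1. The compliance questions ask about booklet lessons and exercises. The satisfaction form has 31 questions on the program and the coach, but for controls: "Participants in the control condition will be asked 11 questions to evaluate their support from the coaches only".

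Blinding. The Design section says: "Participants and coaches will not be blinded to allocation to conditions". It also says that the main researcher cannot see the allocation in advance. Nothing is said about blinding the outcome interviewers.

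**The concern.** The primary outcome is subjective and is taken by live telephone interview. Participants know their arm, so the caller is the one person on that call who could be kept unaware of it. The roles and the T1 content as set out give the caller two routes to the allocation: supervision of the coaches, and the questions in the call itself.

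A caller who expects the program to work may influence the answers, and that influence would tend to favour the intervention. Such a shift adds to the estimated effect in the primary comparison, and neither a larger sample nor the multilevel model corrects it. Part of it is avoidable, and the Trial status section says that recruitment has not started.

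**Working it through.** This is mainly a matter of setting the statements side by side.

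1. **Who collects the outcome.** The researchers do, at T0, T1 and T2 (Procedure; Assessments). The coaches do only the three in-between assessments.
2. **Who supervises.** The researchers and a licensed psychologist do, with recordings and notes used in supervision (Support from a coach).
3. **Do the recordings reveal the arm?** Yes, for any call that is heard. Intervention calls last about 15 minutes and are tied to the six lessons. Control calls last about 5 minutes and ask about well-being.
4. **Does the T1 call reveal the arm?** Yes, by its end. To give the 31-question or the 11-question form, the caller must know or find out the arm. The order of questions within the call is not given. If the depression scales come first, these items do not affect the T1 scores. If they come later, they do.
5. **Does the T2 call reveal the arm?** Not by its content, because Table 1 lists neither compliance nor satisfaction at T2. A caller who did the same participant's T1 interview would already know.
6. **What the stated safeguard covers.** Only the time before allocation. It is allocation concealment and does not reach T1 or T2.
7. **What else protects the scores.** A standard script with questions read as printed, and repetition only at the participant's request.

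**The plan's own figure.** For d = 0.50, alpha = 0.05 (taken as two-sided) and power 0.80, the normal approximation gives 63 per group. The t-test version gives 63.8, which rounds up to the stated 64. That figure is not in dispute.

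**Illustration of what a shift would do.** The document gives no size for interviewer bias, so b = 0.1, 0.2 and 0.3 SD are assumptions. With no true effect and a simple comparison of two means with n per group, the non-centrality is b / √(2/n). The chance of a significant result at two-sided 0.05 is Φ(ncp − 1.96) + Φ(−ncp − 1.96).

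| n per group | b = 0.1 | b = 0.2 | b = 0.3 |
|---|---|---|---|
| 64 (stated requirement) | 8.7% | 20.5% | 39.6% |
| 100 (200 in total, equal arms, no dropout) | 10.9% | 29.3% | 56.4% |

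For example, with n = 64 and b = 0.2, ncp = 0.2 / √(2/64) = 1.131, and the chance is Φ(−0.829) + Φ(−3.091) = 20.5%. The rate rises with n, so recruiting more participants does not help. The table shows how the bias acts. It does not estimate the bias in this trial.

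**The case against.** A reader might infer that the primary outcome will be collected by interviewers who know every participant's arm. The document does not go that far.

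- The overlap is by role and not person by person. The article uses a collective label, and a psychologist shares the supervision.
- The regular coach meetings are with the main researcher only, not with the whole interviewing team.
- Recordings and notes are used to check that coaches follow the protocol. Nothing says that every participant's calls are reviewed.
- The order of questions at T1 is not given and may be fixed in a script that is not shown.
- The roles as written do not rule out blinded callers, because the tasks could be divided among the researchers without contradicting the text.

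All of this stands, and it is why the finding is that callers may know the allocation.

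It is also fair to say that the PHQ-9 and CES-D are self-report items with fixed answers, read as printed to participants who know their arm. A wish to please the program would exist whoever calls. Blinded callers would reduce the bias and not remove it. A reader might also want to state the bias in PHQ-9 points or as a share of the planned effect. The document gives neither an SD nor a size for the shift, so no such figure can be supported.

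The objection that a condensed article is merely silent on assessor blinding does not stand. The article states who interviews, who supervises and which arm-specific questions fall at T1, and those statements together create the exposure.

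**Conclusion.** The concern holds as a risk built into the stated roles and the T1 schedule. Outcome interviewing and coach supervision belong to the same role, the T1 interview contains questions that show the arm, and the only stated safeguard ends at allocation. T1 and T2 callers may therefore know the arm when they read out the depression scales.

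All T1 and T2 primary scores are exposed. The direction would probably favour the intervention, but the size cannot be derived from the document, and the percentages above rest wholly on assumed shifts. The conclusion assumes that the researchers' tasks are not already divided in a document that is not shown. If they are, and the depression scales come first, stating so in the protocol would settle the point. This is a change that should be made because it is cheap and removes an avoidable part of the bias. It does not show that the trial's result would be invalid.

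**What to change.** 1. **Script order.** In the T1 script, ask the PHQ-9 and CES-D first and the compliance and satisfaction items last, opening the arm-specific form only after the depression scores are entered. Begin both the T1 and T2 calls by asking the participant not to mention the booklet or the coach (at T1, until the closing questions).
2. **Division of tasks.** As far as staffing allows, researchers who make T1 and T2 calls do not supervise coaches, attend coach meetings or hear recordings, and work from a call list without allocation. This applies above all to the main researcher, who should not make these calls. Where possible, a different person makes the T2 call from the one who made the T1 call.
3. **Record of unblinding.** Directly after the depression scales, the caller notes whether the allocation has become known. Report this by arm.

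Cost: reordering the script and adding one recorded item take almost nothing. Dividing the tasks costs some scheduling flexibility. The number of researchers is not given, so full separation may not be possible. No extra participants or assessments are needed. Bias from unblinded participants' own reporting remains and should be acknowledged as a limitation.
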